#### Objective 2: Responsive surgical referrals system

A reliable system for monitoring surgical referrals is a critical part of the surgical information system. It can inform decisions about the need to strengthen surgical skills at particular district hospitals from which large volumes of referrals are received at referral hospitals (RHs). Therefore, it is paramount to ensure its correct functioning. However, the team’s previous study (COST-Africa) identified a lack of systematic measures for monitoring flows of surgical referrals. In order to close this data loop, the second objective of our study will be to undertake a quantitative assessment of numbers of surgical referrals sent to RHs within the centre of identified nexuses comprising a group of all district hospitals referring patients to the same central hospital. These nexuses will serve as entry points for delivering and evaluating the supervisory and mentoring intervention.

To strengthen the referral system, a managed clinical network in the form of mobile communicator groups [60, 61] will be established. This will allow for real-time consultations between DLH clinicians and their surgeon supervisors, will facilitate communication prior to referral and will enable the provision of feedback to DLHs once referred patients have received care at the RHs. Data on utilisation of the network will be collected, complementing the data on types of cases referred. The key elements of the planned analysis are summarised in the following table (Table 3).

**Table 3 Tab3:** Overview of objective 2

	Indicators	Data collection instruments	Measurement
Referrals	Number of surgical cases referred by DLHs to RHs Type of surgical cases referred by DLHs to higher level hospitals Key drivers of referrals	Referral data collection tool (monthly review of data from surgical referral registers maintained at the main RHs) PIPES questionnaire	Analysis of changes in referral patterns over time and between intervention and control hospitals
Responsive communications and close referral feedback mechanisms between DLHs and RHs	Frequency of communications via managed clinical support network Timeliness of communications via managed clinical support network	A logbook monitoring communication between DLH clinicians and specialist supervisors	Analysis of utilisation of the managed clinical support networks

To track these changes, the study will collect anonymised aggregated data on a monthly basis from surgical referral registers maintained at RHs. Data fields, as established in the previous project, will include referring DLH, patient age and sex, reason for referral (presumptive diagnosis), pre-referral treatment, cadre of referring clinician, final diagnosis at RH, treatment/procedure and immediate outcome. Data collectors, trained in the project standard reporting format, will be stationed at the main RHs.

A tool to assess the appropriateness of surgical referrals received by RHs from district hospitals will be developed in consultation with local experts; it will be piloted and used to assess the numbers of unnecessary referrals. A designated clinical network manager will monitor communications between DLH surgical teams and between DLHs and RHs/surgical specialists for the duration of the study. For each DLH/RH, research measures will include cadre of communicating health professional, type (call/text), content type (text/picture/results of investigations), frequency, response timeliness and feedback received.

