## Research objectives

The specific objectives of this research study are as follows:To determine whether the intervention is able to affect change in surgical activity at district level. We will assess whether supervision and mentoring will enhance the capacity of district surgical teams, leading to changes in surgical activity. In particular, we expect to observe (1) an increase in the number of procedures regularly performed by the participating hospitals compared to surgical activity before the intervention, as more district clinicians will be trained in handling general surgical procedures and (2) a change in the range of surgical cases done in DLHs as new procedures will be introduced and performed by local teams, where the SOT deems this to be appropriate to local needs, staff skills and resourcesTo establish the feasibility of the intervention to improving skills of local surgical teams (including surgery, anaesthesia and nursing staff) as individuals and as a group. We will test whether the support offered through supervision and mentoring will change confidence (as a proxy measure of skills) and preparedness of local teams in performing essential surgical proceduresTo monitor whether the intervention can change referral practices, particularly whether it can reduce the number of unnecessary surgical cases referred by district hospitals compared to the number before the intervention because skills and confidence of DLHs clinicians are expected to improveTo determine the feasibility and acceptability of the remote consultation mechanism established by the intervention and to assess any changes in communication between DLHs and RHs and in clinical decision-making. The project’s mobile phone-based communication network will give DLH clinicians access to specialist opinion at RHs and will allow real-time consultations with RHs clinicians. The communication network will also facilitate timely feedback to district teams on referred cases

In parallel, the research will investigate process-related aspects of the intervention to determine feasibility and replicability of the proposed regular supervision model, particularly in light of the shortage of specialists at referral institutions and limited budgets. It will identify obstacles and enablers to DLHs supervision done by specialists located at RHs, to build an understanding of what processes need to be put in place for the supervision to be successful in achieving the above objectives.

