#### Intervention hospitals

Intervention district hospitals will receive regular visits from the SURG-Africa SOT. Supervisors will be tasked with attending surgical outpatient clinics, conducting ward rounds with DLH surgical clinicians, reviewing theatre management practices, delivering in-service training (including hands-on supervision of elective surgical cases done by the local surgical teams), reviewing post-operative cases and liaising with hospital management to facilitate improvements in surgical care delivery. The in-service training will focus on building the necessary skills and attitudes to deliver safe surgery, appropriate to the district level of care, including among others:Clinical decision-making, when to operate, when to observe and when and how to refer the surgical patient to the next level of care (regional or zonal hospital)Safe anaesthesia, peri- and post-operative monitoring of surgical patientsSafe surgery for elective and common emergency conditions appropriate at district levelAudit and quality assurance processes

Quarterly hospital visits will last two full days, with schedules determined at PAR workshops that bring together key stakeholders (i.e. DLH staff, specialists at referral hospitals, representatives of professional associations and ministries of health) in each of the target countries. Planning of activities will be agreed jointly between SOT and DLH staff ahead of each visit. The aim is to develop a bespoke intervention in each country, addressing the specific local needs of each participating hospital through a series of consultations between DLH staff and their supervisors. Additionally, specialists will provide on-call support to district-level surgical staff from the designated intervention hospitals as needed (e.g. in case of uncertainty about diagnosis, clinical aspects of individual patients requiring surgery, operative and referral decisions, etc.) through a mobile phone-based network.

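### Referral counts come month by month only from the main referral hospitals' registers, so a change in where patients are sent could look like a change in referring

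*Protocol article*

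**What the plan says.** The aim is broad. The Research objectives ask whether the intervention can "reduce the number of unnecessary surgical cases referred by district hospitals", with no destination named. The Abstract (Methods) and the Study design section likewise describe referral to higher care in general.

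The measurement is narrower. Table 3 gives two indicators one after the other, "Number of surgical cases referred by DLHs to RHs Type of surgical cases referred by DLHs to higher level hospitals"; the first is limited to RHs and the second is not. The text of Objective 2 describes the quantity as "numbers of surgical referrals sent to RHs within the centre of identified nexuses comprising a group of all district hospitals referring patients to the same" (the sentence ends by naming the hospital that the group shares). The register source in Table 3 is a "monthly review of data from surgical referral registers maintained at the main RHs", and the text adds: "Data collectors, trained in the project standard reporting format, will be stationed at the main RHs". The planned appropriateness tool, meant to count unnecessary referrals, is applied to referrals that RHs receive.

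Table 3 also lists the PIPES questionnaire for this row. According to Objective 1, its annex covers referral patterns at facility level, at baseline, month 12 and month 24.

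The section on intervention hospitals lists, among the training topics, "when and how to refer the surgical patient to the next level of care (regional or zonal hospital"), which suggests that a district hospital may have more than one possible destination.

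**The concern.** A register kept at a receiving hospital shows only what arrives there. If a district hospital sends some surgical patients to other higher-level hospitals, those cases are missing from both the count and the appropriateness assessment.

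A constant loss would matter little for a before-after comparison. A changing one would matter, and the intervention acts on the decision concerned: in-service training covers referral, and the phone network lets district clinicians consult RH specialists before referring. A clinician who has just spoken to a surgeon at the main RH may send there a patient who would formerly have gone elsewhere, or may be advised to use another hospital. In either case the main-RH count moves without any change in how many patients are referred.

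The control arm does not remove this. Control hospitals have no oversight-team visits, are outside the on-call network and refer to different RHs. At stake is the reading of Objective 2: whether the district hospitals referred fewer patients, or the main RH received fewer.

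**Working it through.** The protocol states no referral count, rate or destination share, so there is no figure of its own to reproduce. The check compares definition with source and then illustrates the size under assumed shares.

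**1. Definition against source**

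| Place | Destination covered |
|---|---|
| Abstract (Methods), Study design | higher care in general |
| Research objectives | none named |
| Objective 2 text | RH at the centre of the nexus |
| Table 3, number of cases | RHs |
| Table 3, type of cases | any higher-level hospital |
| Monthly registers, data collectors | main RHs |
| Appropriateness tool | referrals received by RHs |
| PIPES annex, three time points | referral patterns; items not shown |

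The aims and the type indicator are wider than the only monthly source.

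**2. Size when total referrals do not change**

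Let p0 and p1 be the shares of a hospital's surgical referrals that go to the main RH before and after. The apparent change in the main-RH count is p1/p0 − 1. All shares below are assumptions.

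- p0 = 0.80, and half of the remaining 0.20 moves in: p1 = 0.90, and 0.90/0.80 − 1 = +12.5%.
- p0 = 0.80, with the same 10 points moving out: 0.70/0.80 − 1 = −12.5%.
- A 10-point shift from p0 = 0.50 gives ±20%; from 0.70, ±14.3%; from 0.90, ±11.1%; from 1.00, −10% (only outward movement is possible).
- p1 = p0 gives 0%.

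**3. Size when referrals truly fall**

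Let s be the share sent elsewhere at baseline, f the fraction of that share that moves to the main RH, and r the true fall. The ratio of the main-RH count after to before is (1 − r)(1 − s + s·f)/(1 − s).

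| s | f | r | Ratio | Reads as |
|---|---|---|---|---|
| 0.20 | 0.5 | 0.10 | 0.90 × 0.90/0.80 = 1.0125 | about +1% |
| 0.20 | 0.5 | 0.20 | 0.80 × 0.90/0.80 = 0.90 | −10% |
| 0.10 | 0.5 | 0.10 | 0.90 × 0.95/0.90 = 0.95 | −5% |
| 0.30 | 0.5 | 0.10 | 0.90 × 0.85/0.70 = 1.093 | about +9% |

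A true 10% fall changes sign only if s·f/(1 − s) exceeds 0.10/0.90 = 0.111. With s = 0.10, even a complete shift (f = 1) gives 0.10/0.90 = 0.111, which only reaches that boundary.

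**4. Controls**

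If the destination share is stable in the control hospitals, their artefact is zero and the intervention arm's artefact passes in full into the between-arm comparison of changes.

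**The case against.** The other side has good points, and several of them stand.

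- The Objective 2 text does say what is counted: referrals to the RH at the centre of the nexus. The count indicator agrees with it, so the type indicator may just be loosely worded. This stands, and it is a reason to relabel the outcome. It does not reconcile the narrower count with the wider aims.
- A reader might infer that the plan defines referrals by three competing destinations. It does not. The indicators use two terms; the regional or zonal wording is training content, and the document does not say how such hospitals relate to the main RHs.
- A reader might infer that nothing but the main-RH registers is consulted. That goes too far. PIPES is a listed instrument and its annex covers referral patterns. The annex is not shown, so a destination item may already be there. Even so, it gives three time points against a monthly count, and the text does not link the two.
- Nothing states that the network redirects patients. Intervention hospitals must lie within the designated network of a named RH, which limits leakage. A shift is therefore possible, not established.
- The qualitative component will look at patient flows and drivers of referral. It could help to reveal a large shift but would not quantify it.
- Referrals are not the primary endpoint, and the study is an exploratory pilot. This limits the weight of the point, though the results are meant to guide national scale-up.

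**Conclusion.** The point holds as a mismatch between what the plan wants to conclude (fewer unnecessary referrals by district hospitals) and what its monthly source can show (referrals arriving at the main RHs). A change of destination in the intervention hospitals could appear as a change in referring, and the control arm would not cancel it.

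Size and direction are unknown. The 12.5% figure rests on two assumed inputs: 20% sent elsewhere at baseline and half of these moving to the main RH. If the destination share does not change, there is no artefact. A reader might conclude that the referral result is likely to have the wrong sign; the documents do not support this, since a reversal needs particular combinations of share, shift and true effect.

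The matter is worth settling in the protocol, because where the data are collected is fixed there. A destination that is never recorded cannot be recovered by later analysis.

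**What to change.** 1. Use one destination term for both referral indicators in Table 3.
2. Label the register outcome as referrals received at the main RH, and limit conclusions, including those from the appropriateness tool, to that.
3. Make sure the PIPES annex records, at months 0, 12 and 24, the share of each district hospital's surgical out-referrals by destination.
4. Report that share next to the register count, by arm, and claim a change in total referrals only when the share is stable.

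Scaling the monthly count by the share is at most a sensitivity analysis, since it brings in the error of the share.

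The cost is a wording change and, if it is not already there, one annex item; no new data collectors are needed. The downside is that the share rests on staff report or district records at three time points, so it can expose a sizeable shift but cannot correct the monthly series precisely.

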#### Objective 3: Qualitative assessment of the intervention: obstacles and enablers

The third element of our study involves a qualitative assessment to obtain a better understanding of the functionality of DLH surgical systems (capacity building, decision-making, staff motivation, communications with higher levels, etc.) and how these have been influenced by the intervention. It will also provide further information on the feasibility and impact of the supervision model implemented by the project and will help inform the future scaling up of the intervention under the leadership of local MoHs.

The analysis will look at, but not be limited to, the following:Defining what types of elective and emergency surgery can be delivered at what levels—first referral and specialist hospital, by what staff and under what conditions. Questions include the following: What is the (or is there a) national policy for each level? Are there policies/regulations on what types of cases can be delivered at district hospitals, and can agreement be reached with the national stakeholders—MoH, Medical Council and national surgeons—on what cases can be delivered by district-level clinicians, subject to what conditions—training, supervision, etc.?Gaining insight into how health-seeking behaviours, population preferences and patient flows to particular hospitals shape the demand for surgery in district communitiesDetermining what are the main obstacles and enablers to surgical service delivery at facility level, and how these can be addressedIdentifying opportunities to establish more effective referral systems, including key drivers of referrals and any changes/improvements attributable to the intervention (e.g. looking at protocols, communication and information systems for district clinicians to consult with surgeons, transport patients and get feedback from referring hospitals)In-depth exploration of the appropriateness and potential sustainability of the proposed model, its impact on work practices, staff confidence, attitudes etc. by investigating participants’ experiences of taking part in the supervision and support networkAssessing the functionality of the support network, and its responsiveness, by analysing participants’ experiences of the clinical support network

The qualitative part of our study will involve semi-structured interviews and focus group discussions (FGDs) with key informants at district, regional, zonal and national levels. District staff may include district medical/health officers; hospital managers and members of the DLH (district-level hospital) surgical team, comprising NPCs, GMOs and nursing staff, covering surgery, anaesthesia and post-op nursing. As a general guide, three staff members are to be interviewed at each DLH, so the total sample will include at least 30 respondents per country. At regional/zonal level, relevant staff may include medical/health officers, referral hospital managers and members of the SOT, including specialists in surgery, anaesthesia, and nursing at the RHs. FGDs and in-depth interviews will be conducted at two points in the life span of the project. Interviews and focus groups will be conducted by the research team. Respondents will be identified by the district medical officers (DMOs) or Theatre In-Charge, and none of the researchers is directly related to participants. All interviews will be anonymous and responses will be analysed in cumulative form. These measures will minimise the risk of bias in the responses.

While each of the three study objectives is treated as a stand-alone for presentation purposes, in practice, they are closely linked and overlapping, with the qualitative assessment, in particular, cross-cutting the other two. We do not expect change to be homogenous across all indicators, but rather expect that while the intervention may be successful at changing some dimensions of district-level surgical capacity, it may fail to do so on other dimensions. However, the expected result of the intervention is a trend that indicates a positive change in the abilities of DLHs to deliver more surgeries. This trend may not be observed in all facilities receiving the intervention.

### Sample size

The hospitals to be considered for inclusion will be selected from the pool of eligible (i.e. surgically active and accessible) hospitals in each geographical area covered by the research, as follows:Malawi: 22 eligible hospitals out of 24 public district hospitals in the countryZambia: 27 eligible hospitals out of 99 Level 1 (district) hospitals in the countryTanzania: 36 eligible hospitals out of 41 district health facilities in the Northern Zone (comprising of Manyara, Tanga, Singida, Arusha and Kilimanjaro regions)

Study design and sample size are dictated by local realities (i.e. number of hospitals eligible to receive the intervention as well as the limited availability of qualified supervisors who can commit themselves to deliver sufficient numbers of visits). Nevertheless, the study will select as many eligible hospitals as possible for its sample in order to ensure country and cross-country representativeness.

### Data analysis

The analysis plan comprises comparison of the changes from baseline to end of study (after 24 months of the intervention) in primary and secondary endpoints. The analysis will involve descriptive and summary statistics (frequency counts) for the quantitative data and comparisons of means (with the relevant parametric or non-parametric test), where before-and-after changes are expected. Results will be presented with 95% confidence intervals. Significance will be set at 5%, two-tailed. We intend to have multiple time-points at which data will be collected. Repeated measures will be made to analyse trends in the primary and secondary outcomes, making the assumption that any secular trends (government investments, staff deployments, etc.) will occur irrespective of the allocation of hospitals to either intervention or control arms of the trial. However, even if this is not the case, important secular activities and events will be captured through the qualitative study phase. This is particularly important in LMICs where attention to surgery is growing and other externally-driven activities may take place [6]. The qualitative data will be analysed using the ‘top-down’ method of theme identification [62].

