It is expected that the intervention will change the *surgical productivity* of DLHs in terms of number of common surgical procedures performed and types and numbers of new procedures introduced, which form the primary endpoint of the study. Monthly numbers of Caesarean sections are typically used to assess the volume of major surgery at DLHs. SURG-Africa will monitor this parameter and include a larger set of core general surgical procedures done in DLHs, identified through the initial situation analysis. This will allow us to develop an index of key procedures to compare differences in numbers and types of procedures: (1) before and after and (2) between intervention and control hospitals, at both group and individual hospital level of analysis. In parallel, the evaluation will track intra-hospital mortality rates to monitor possible changes in surgical outcomes as surgical activity is expected to increase.

Our study will also analyse whether the intervention will result in changes in the key drivers of DLH productivity, namely the *capacity* of local surgical teams and overall *preparedness* of the facilities to perform surgery. The change in staff capacity will be measured through a before-and-after controlled comparison of the number of intervention DLH staff who is reported as competent in doing index procedures. Another measure is self-reported surgical confidence as a proxy parameter for surgical skills. This tool has been tested and validated by previous studies, showing positive correlation between confidence of surgical providers and assessment of skills by their supervisors [57].

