Another important aspect of our research is the use of a PAR approach in the development and refinement of the model. The PAR approach will allow us to build a good understanding of what works and what does not work on the ground; it will facilitate the establishment of a trust-based relationship among collaborators and will ensure a sense of ownership among partners and stakeholders involved in the implementation of the project in the participating countries. SURG-Africa was designed as a *health systems trial*, similar to that described by Sando et al. [66]. Firstly, the intervention is being implemented through public sector systems in Tanzania, Malawi and Zambia, incorporating three large geographical areas in the target countries for testing the solutions to be scaled up under the leadership of local ministries. Secondly, the intervention is being delivered by government-employed members of the SOT, as part of what is supposed to be their routine duties as qualified surgeons. The difference between the proposed SURG-Africa model and the usual activities conducted by surgeons when occasionally visiting DLHs is that, in our model, the emphasis is on capacity building rather than on clearing theatre waiting lists in rural facilities [67]. So-called outreach campaigns organised either by MoHs or donor-funded projects are considered to be effective in achieving their goals; however, evidence of this is limited [68]. Moreover, they cannot be regarded as sustainable means of increasing capacity at district level to deliver surgical services when needed [6, 69], and there is a concern about the ethics of such interventions if led by foreign specialists [70].

The ultimate goal of SURG-Africa is to engage local stakeholders and produce a sustainable solution which is developed, implemented and owned locally. To our best knowledge, there has not been any published study looking at strengthening DLHs surgical capacity, mobilising existing resources through a programme of regular supervisory visits that includes mentorship, supervision and hands-on training for already practicing surgical care providers. SURG-Africa aims to fill this gap. The expected result is an evidence-based supervision model ready for national scale-up in the participating countries, championed by ministries of health. Through dissemination activities, we aim to transfer lessons learned in Malawi, Zambia and Tanzania to other SSA countries interested in investing in rural surgical services.

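### The pooled comparison of changes has no country term, although the non-randomised arms are built separately within three countries and the control numbers per country are open

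*Protocol article*

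**What the plan says.** In the protocol article, Data analysis sets out a "comparison of the changes from baseline to end of study (after 24 months of the intervention) in primary and secondary endpoints". The method named is "comparisons of means (with the relevant parametric or non-parametric test), where before-and-after changes are expected", with 95% confidence intervals, and "Significance will be set at 5%, two-tailed". The same section mentions repeated measures for trends and assumes that secular trends, such as government investment and staff deployment, arise regardless of arm.

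Under Objective 1, the primary endpoint is the number of common procedures together with "types and numbers of new procedures introduced, which form the primary endpoint of the study". The arm comparison is to be made "between intervention and control hospitals, at both group and individual hospital level of analysis". Country is not one of the listed levels.

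The design, in contrast, is organised by country:

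- Table 1 (Intervention and control hospitals) gives each country its own regions and its own selection rules for each arm.
- Research sites rules out randomisation, claims that district hospitals are fairly alike inside each country, and leaves the choice of controls to the situation analysis.
- Intervention hospitals says: "The aim is to develop a bespoke intervention in each country".
- Sample size gives the eligible hospitals as 22 in Malawi, 27 in Zambia and 36 in Tanzania. It states no number of controls.

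**The concern.** In a non-randomised comparison the credible contrast is the one made inside the unit where the arms are said to be alike. Here that unit is the country, because no likeness across countries is claimed. Investment and staffing policy are plausibly national matters, so change over 24 months could differ between countries even if it is the same in both arms within each of them.

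Two things are then at stake. Country differences in change enter the error term of a pooled comparison of means and reduce power. If one arm draws more of its hospitals from a particular country, those differences also enter the estimate. The article's assumption that secular trends do not depend on arm protects the contrast within each country. It does not protect a pooled contrast between arms with different country mixes.

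**Working it through.** **The plan's own figure.** There is none to reproduce. The article gives no power, effect size or standard deviation, and it says the sample size follows from local circumstances. The numbers below are illustrations.

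**Inputs**

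- Intervention hospitals: 30 in three countries (Research sites).
- Per country: about 10. This is an inference from 30/3 = 10 and from Objective 3, where three interviews per hospital give at least 30 respondents per country (30/3 = 10). It is not stated directly.
- Eligible hospitals: 22, 27 and 36 (Sample size).
- Controls: not stated. Two cases are taken: 10/10/10, and all remaining eligible hospitals, 22−10 = 12, 27−10 = 17 and 36−10 = 26, total 55.

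**Bias of the pooled difference.** Let the secular change in country k be m_k, the same in both arms. Without a country term, the bias is the sum over countries of (intervention weight − control weight) × m_k.

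- Control weights in the second case: 12/55 = 21.8%, 17/55 = 30.9%, 26/55 = 47.3%. Intervention weights: 33.3% each.
- Only Tanzania differs, by D: (0.333 − 0.473) D = −0.14 D.
- Changes of −s, 0 and +s in Malawi, Zambia and Tanzania: (0.333 − 0.218)(−s) + (0.333 − 0.473)(s) = −(26 − 12)s/55 = −0.255 s. For s = 0.5, 1.0 and 1.5 SD this is −0.13, −0.25 and −0.38 SD.
- With 10/10/10 controls all weights are equal and the bias is zero.

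The sign depends on which country changes more.

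**Precision with equal mixes.** The variance of −s, 0, +s is 2s²/3. With a within-country SD of change of 1, the error variance used by the unadjusted test rises by the factor 1 + 2s²/3: 1.17, 1.67 and 2.50 for s = 0.5, 1.0 and 1.5.

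**Simulation.** 20,000 trials per scenario, within-country SD 1, true effect 0.73 SD where power is shown.

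| Controls | s | Power, no country term | Power, country term | Null rejection, no country term | Null rejection, country term |
|---|---|---|---|---|---|
| 10/10/10 | 0 | 0.80 | 0.80 | 0.048 | 0.049 |
| 10/10/10 | 0.5 | 0.75 | 0.79 | 0.034 | 0.049 |
| 10/10/10 | 1.0 | 0.59 | 0.79 | 0.010 | 0.047 |
| 10/10/10 | 1.5 | 0.36 | 0.79 | 0.002 | 0.052 |
| 12/17/26 | 0.5 | 0.69 | 0.88 | 0.063 | 0.050 |
| 12/17/26 | 1.0 | 0.32 | 0.88 | 0.082 | 0.048 |
| 12/17/26 | 1.5 | 0.06 | 0.89 | 0.078 | 0.050 |

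The simulated bias without the country term in the 12/17/26 null case was −0.13, −0.26 and −0.38 SD, in line with the formula. With the country term it was at most 0.004 SD in magnitude.

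**The case against.** **Silence is not exclusion.** The article does not rule out a country term, and a fuller analysis plan that is not shown may contain one. It would be wrong to say that the investigators decided to ignore country. What remains is that the article itself fixes the endpoint, the time contrast, the type of test and the levels of comparison, "at both group and individual hospital level of analysis", and country is missing from that list although the design rests on it.

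**Change scores already help.** Stable differences in level between countries cancel in a change from baseline. This stands: only differences in change matter, and the documents give no figure for them. At s = 0 the country term gains nothing. With equal mixes, leaving it out makes the test conservative and does not create false claims.

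**The 12/17/26 case is not a forecast.** Sample size says as many eligible hospitals as possible will be taken, but controls are also screened on PIPES score, productivity and staffing. The eventual mix could be closer to balance or further from it.

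**A stronger reading that does not hold.** Because the interventions are country-specific and the Discussion says "The expected result is an evidence-based supervision model ready for national scale-up in the participating countries", a reader might infer that the plan leaves open whether the pooled result or a country result decides, with several 5% tests competing. The documents do not support this. No section announces a significance test per country or a success rule that turns on one. Control hospitals describes two groups followed and compared, Study design calls the work exploratory, and the article presents itself as a pilot of feasibility. Error rates for tests that nobody plans are therefore no criticism of it.

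**Conclusion.** The point holds as a matter of method. For arms assembled without randomisation inside three countries, a country-stratified comparison of changes is better than the comparison of pooled means that the article describes. It matches the article's own argument about homogeneity and its assumption about secular trends.

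The size is conditional. It is nil if changes do not differ by country. If they do, equal mixes cost precision only, and unequal mixes also bring bias of about 0.14 D in the illustrated case. These figures rest on 10 intervention sites per country, the two assumed control mixes, an assumed effect of 0.73 SD and assumed country differences in change. None of the last three comes from the documents. For an exploratory pilot this is an inexpensive improvement and not a flaw that invalidates the study.

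**What to change.** In Data analysis, state that the between-arm comparison of hospital-level changes is stratified by country: country as a fixed effect in the parametric analysis, or a non-parametric test stratified by country. State also that the three country estimates will be reported with 95% confidence intervals as supporting, descriptive results. That is useful because the intervention may differ between countries, so the pooled figure is an average.

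The cost is two degrees of freedom (from 58 to 56 with 30 versus 30 hospitals), one or two sentences, and no new data. The scale-up wording in the Discussion need not change.
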